#### 2.3.2. Data management.

Data from this study will be collected and managed using REDCap electronic data capture tools hosted at Maisonneuve-Rosemont hospital. Research staff will systematically double-check all data entries for completeness and accuracy before final submission. Each participant will be assigned a unique identification number upon enrollment to maintain confidentiality and ensure anonymization.

All collected data will be securely stored on a designated research computer, which will remain offline and be located in a restricted area in Maisonneuve-Rosemont hospital. Notably, this computer will utilize the integrated event-tagging system of the PMD-200 or the BetterCare software (provided by Dräger, Lübeck, Germany), which is connected to the Dräger anesthesia workstation. Usage of this computer will be limited to authorized research personnel, who will need encrypted logins to access study data.

To promote data quality, double data entry will be implemented for our primary outcome. Furthermore, regular, informal audits will be conducted by the research team to verify the accuracy of the study data.

After study completion, electronic data will be retained on secure, encrypted servers for a period of 7 years, as per local institutional and ethical guidelines. Physical copies of patient information, such as consent forms, will be securely stored in a locked file cabinet in the anesthesiology department.

#### 2.3.3. Statistical methods.

Descriptive statistics will be used to summarize the data by group. Primary outcome and secondary continuous parameters will be presented as means with standard deviations, or medians with interquartile ranges if the data is skewed or non-normally distributed. Categorical variables will be reported as frequencies (%). 95% confidence intervals (CIs) for proportions or mean/median differences will be presented based on the type of endpoint analyzed, and statistical significance will be determined using an alpha level of 0.05. Parametric, two-sample t-tests will be performed for normally distributed outcomes. Otherwise, a non-parametric Wilcoxon test will be performed.

Univariate analyses will be performed to explore relationships between the primary outcome (total propofol consumption) and other potential variables. Variables showing significant associations (P < 0.05) or clinical relevance will be considered for inclusion in a multivariable linear regression model. To evaluate the fit of our linear regression models, we will examine R^2^ and adjusted R^2^ values to assess explanatory power. In addition, residual plots and diagnostic statistics will be used to evaluate assumptions of linearity, normality, and homoscedasticity. If model fit is inadequate, appropriate transformations or alternative modeling strategies will be considered. Logistic regression may be employed where appropriate for binary secondary or exploratory outcomes. To evaluate the fit of our logistic regression models, we will conduct the Hosmer-Lemeshow goodness-of-fit test; P > 0.05 will be considered indicative of an adequate model fit. If poor fit is detected, alternative modeling strategies, such as transformations or interaction terms, will be considered.

Subgroup analysis will also be performed to explore how the selected initial VR scenario may impact our primary outcome. In the case of conversion to general anesthesia, the participant will be considered a protocol deviation. These participants’ data will still be included in the final analysis following an intention-to-treat (ITT) approach. Additionally, we will compare the prevalence of protocol deviations between the intervention and control groups to assess whether the conversion rate differs between conditions. To minimize protocol deviations, patient recruitment and randomization will only be finalized after the paravertebral block has been performed and its effectiveness has been confirmed by the lead clinician. If the block is deemed grossly ineffective, the patient will not be recruited or randomized.

As part of our exploratory analysis, we will investigate the relationship between the NOL index and propofol self-administration to determine whether NOL spikes serve as a predictor of subsequent propofol boluses. To achieve this, we will define a spike as any NOL score exceeding a threshold of 50 for a pre-specified duration of at least 10 seconds. We will then use time-series analysis to assess the temporal relationship between NOL spikes and propofol bolus administration. This will allow us to apply logistic regression and/or time-to-event analysis to determine whether NOL spikes significantly predict the likelihood of a propofol bolus within a predefined timeframe of up to 60 seconds.

All statistical analyses will be conducted using SAS, SPSS, or Python programming language with VS Code or Jupyter Notebook software.

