### 1.2. Objectives and hypotheses

The primary objective of this study is to determine if intraoperative virtual reality immersion reduces the use of self-administered propofol for patients undergoing breast surgery under paravertebral (PV) block.

Our secondary objectives are the following

Determine the participants’ initial enthusiasm at the idea of using a VR headset during surgery.Evaluate the level of anxiety and information requirement before the surgery, as they could act as potential confounders if randomization does not adequately balance groups;Evaluate the incidence of adverse effects such as cybersickness, nausea, bradycardia, desaturation, and hypotension;Evaluate the time the patient spent wearing the headset;Evaluate the differences in sedation requirements depending on the type of VR scenario.Evaluate need for additional local anesthesia;Evaluate quantities of fentanyl administered;Evaluate quantities of ketamine administered;Evaluate the requirement of post-operative care and the post-anesthesia monitoring time;Determine the ease of use of the technology, enjoyment of the first scenario chosen and overall satisfaction with the experience.

This trial also has an exploratory objective, which is to investigate the use of the Nociception Level (NOL) index in awake patients undergoing surgery, and the ability to anticipate sedation self-administration via the NOL index.

Regarding our primary objective, we hypothesize that patients undergoing breast surgery under PV block with an immersive VR experience will self-administer less propofol than the control group. We also hypothesize that interactive scenarios will further reduce the requirement for sedation, when compared to non-interactive scenarios.

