#### 2.1.6. Sample size.

The available literature on sedation requirements for adult patients using intraoperative VR headsets during surgeries under regional anesthesia is limited and heterogeneous, with studies reporting up to 93% reductions in sedation requirements [19], and others reporting no significant changes [20]. However, in a study evaluating lidocaine as an adjunct to reduce propofol requirements during pediatric colonoscopy, the lidocaine group consumed 35.5% less propofol than the control group, which was associated with significantly shorter awakening times, faster recovery times, and fewer involuntary movements during the procedure [21]. Similarly, a study comparing PCS to clinician-controlled sedation found a 39.3% reduction in propofol usage in the PCS group, which correlated with fewer episodes of deep sedation, fewer airway and breathing adverse events, and faster recovery times [22]. Therefore, for our sample size calculation, we estimated a 30% reduction of propofol usage in the VR group compared to the control group to be an approximate threshold for clinical significance. A two-sample t-test was used for the calculation, with a two-sided hypothesis test and a significance level of 0.05. To achieve 80% power, 90 participants were required, with the sample size inflated to 100 to account for attrition (e.g., dropout, protocol deviations).

Paravertebral block with propofol sedation has been validated as a safe and effective alternative to general anesthesia for breast cancer surgery, offering benefits such as higher turnover rates, reduced postoperative nausea, and faster hospital discharge [23]. According to historical data by Sessler et al., patients undergoing breast surgery with paravertebral block received a median propofol dose of 525 mg per patient [14].

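### The regression's covariates are chosen by P < 0.05 or undefined clinical relevance and need not be baseline variables, while the main comparison forgoes adjustment for preoperative anxiety

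*Protocol article*

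**What the plan says.** Section 2.3.3 (Statistical methods) sets the group comparison as a two-sample t-test for normally distributed outcomes and a Wilcoxon test otherwise. Neither uses covariates. The sample size in section 2.1.6 rests on the same test: "A two-sample t-test was used for the calculation".

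Section 2.3.3 then plans univariate analyses relating the primary outcome to further variables that it does not name, followed by this rule: "Variables showing significant associations (P < 0.05) or clinical relevance will be considered for inclusion in a multivariable linear regression model". It does not define clinical relevance, limit candidates to variables measured before allocation, or rank the regression against the t-test or Wilcoxon test.

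The preoperative anxiety score (APAIS) is to be measured in all participants (sections 2.1.4 and 2.3.1). Section 1.2 explains why anxiety and information need are measured: "as they could act as potential confounders if randomization does not adequately balance groups".

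**The concern.** Two separate things are at stake.

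First, bias in any adjusted VR effect. Section 2.1.4 lists intraoperative fentanyl and ketamine among the outcomes. Both arise after allocation, VR could change them, and they plausibly track propofol use. A screen on association with the outcome favors such variables. Conditioning on one of them in a model that also contains arm can take away part of the effect the trial is meant to estimate.

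Second, precision. The trial tests an anxiolytic mechanism and measures anxiety before surgery, so APAIS anxiety is a natural prognostic covariate. The main comparison does not use it, and whether the regression does is left to an observed P value or to judgment.

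**Working it through.** **Inputs from section 2.1.6.** Error rate: "with a two-sided hypothesis test and a significance level of 0.05". Size: "To achieve 80% power, 90 participants were required, with the sample size inflated to 100 to account for attrition". Effect: "we estimated a 30% reduction of propofol usage in the VR group compared to the control group". Allocation is 1:1 (section 2.2), so 45 per arm. No SD is given, only a historical median of 525 mg, so the standardized effect has to be solved backwards.

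**Step 1. The plan's own figure.** A two-sided t-test at 0.05 with 45 per arm has 80% power at d = 0.597. With a 30% reduction this implies a coefficient of variation of 0.30 / 0.597 = 0.50. The stated 90 is consistent with that unstated value; it neither supports nor weakens this point. Below, d = 0.597 is the unadjusted effect.

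**Step 2. Adjusting the main comparison for APAIS anxiety.** Let r be the within-arm correlation of anxiety with the propofol rate. The documents give none, so r = 0.2 to 0.5 is assumed. Residual variance is multiplied by 1 − r², the effect becomes d / √(1 − r²), and the equivalent sample is 1 / (1 − r²) times as large.

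| r (assumed) | 1 − r² | d / √(1 − r²) | Power, 45 per arm | Equivalent sample |
|---|---|---|---|---|
| 0 | 1.00 | 0.597 | 80% | 1.00 |
| 0.2 | 0.96 | 0.609 | 82% | 1.04 |
| 0.3 | 0.91 | 0.626 | 84% | 1.10 |
| 0.4 | 0.84 | 0.652 | 86% | 1.19 |
| 0.5 | 0.75 | 0.690 | 90% | 1.33 |

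The one degree of freedom spent on the covariate is ignored.

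**Step 3. Would anxiety pass the screen?** By Fisher's z with N = 90, the chance is Φ(√87 · atanh r − 1.96) plus a negligible lower tail: 47% at r = 0.2, 82% at 0.3, 98% at 0.4 and over 99% at 0.5. Where adjustment matters most, anxiety would usually be selected. Where it would often be missed (r = 0.2), the gain is only about 2 points.

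**Step 4. Cost of screening with baseline candidates only.** Simulation: 90 patients, 10 baseline candidates of which one is prognostic, 10,000 runs.

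| | Unadjusted | Pre-specified adjustment | Screened model |
|---|---|---|---|
| Type I error, r = 0.3 | 4.9% | 4.8% | 4.7% |
| Type I error, r = 0.5 | 4.4% | 4.4% | 4.6% |
| Power, r = 0.3 | 79.9% | 82.8% | 81.2% |
| Power, r = 0.5 | 80.2% | 89.7% | 89.0% |

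The screen costs 82.8 − 81.2 = 1.6 points or 89.7 − 89.0 = 0.7 points and leaves type I error near its nominal level. Only if the better of the unadjusted and screened results were reported would type I error rise, to 6.2% (r = 0.3) or 6.6% (r = 0.5).

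**Step 5. One post-randomization variable among the candidates.** Suppose a variable such as fentanyl dose has an assumed within-arm correlation of 0.5 with the outcome and shifts with it between arms. Adjusting for it alone leaves 0.597 × (1 − 0.5²) = 0.448 SD. In the simulation at r = 0.3, with this variable added to the 10 candidates, the mean screened estimate was 0.447 SD and power 69%, against 82.8% for the pre-specified model. Type I error of the screened model stayed at 5.4%. The harm is a diluted effect, not false positives.

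**The case against.** The strongest reply is that the main result is untouched. The t-test or Wilcoxon test comes first and the trial is sized on it. The regression follows univariate analyses of an exploratory kind, and the text never says that arm is a term in it or that it replaces the main test. An unadjusted primary test is valid, and a covariate list is commonly left to a SAP, which is not shown. All of this stands. It confines the bias to the case where the model is used to report an adjusted VR effect. It does not clear the rule itself: the protocol does more than omit a list, because it states how covariates are chosen, and a SAP that followed it would inherit the open candidate set.

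Four stronger readings are tempting, and the document does not support them.

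- *Anxiety must pass P < 0.05, so the score is wasted.* The rule has a second route, clinical relevance, by which anxiety could enter without passing any screen. That route is undefined, so it adds discretion, but it is there.
- *Section 1.2 makes adjustment depend on observed imbalance.* It gives a reason for measuring anxiety; it sets no analysis rule.
- *Screening makes the standard errors for the VR effect too small.* With baseline candidates, step 4 shows no inflation. Inflation needs selective reporting of the better result, which the protocol does not propose.
- *Headset time could enter as a covariate.* It applies only to the VR arm, so it is an implausible term in a two-arm model. Fentanyl and ketamine are the realistic examples.

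**Conclusion.** The point holds in a limited form. The covariate rule is poorly fixed for any model that estimates the VR effect, because it admits variables arising after allocation. Under an assumed correlation of about 0.5, one such variable reduces the effect by about a quarter (0.60 to 0.45 SD) and power to about 69%. Whether this happens depends on how the regression is used, which the article does not say.

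The more certain loss is precision forgone in the main comparison: about 2 to 10 power points for assumed correlations of 0.2 to 0.5. That rests on the effect implied by the plan's own 90 patients and on a roughly linear relation between anxiety and propofol rate. Screening among baseline variables is a minor matter of about 1 to 2 points.

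A reader might infer that the primary P value is compromised. It is not. This is a change that should be made, not a flaw that invalidates the primary analysis.

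**What to change.** In section 2.3.3:

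1. Drop the P < 0.05 screen for any model that estimates the VR effect.
2. Pre-specify one linear model of the primary outcome as defined in section 2.1.4 (self-administered propofol, mcg/kg/min) on arm plus baseline APAIS anxiety, with robust standard errors. Make it the named adjusted analysis, run whether or not the arms look balanced. Naming the outcome this way also settles the mismatch with section 2.3.3, which describes the primary outcome as total consumption.
3. Admit only covariates recorded before randomization. Type of surgery may be added only if it is recorded before allocation.
4. State in advance how this analysis ranks against the unadjusted test.
5. Keep the univariate and multivariable search for predictors if wanted, labeled exploratory only.

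The cost is slightly more wording and analysis work. APAIS is already collected preoperatively, so no patients, visits or measurements are added.

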Pharmacological sedation is a crucial part of awake medical procedures, primarily aimed at providing anxiolysis and, when necessary, amnesia. However, these medications can have serious side effects, such as respiratory depression, especially when used alongside opioid analgesics [12]. In fact, research suggests a dose-dependent relationship between the amount of procedural sedatives administered and the length of recovery times in the post-anesthesia care unit (PACU) [13]. This highlights a critical gap in the current literature, as VR could be a low-risk adjunct or alternative to procedural sedation. This is especially relevant for breast surgeries performed only under regional anesthesia, which is increasingly recognized as a valid alternative to general anesthesia. Notably, this approach has been shown to be equivalent to general anesthesia in terms of breast cancer recurrence and persistent incisional breast pain, but often necessitates substantial sedative use, creating an opportunity for VR to potentially reduce sedation requirements [14].

Finally, the Nociception Level (NOL) index is a technology developed by Medasense Biometrics Ltd (Ramat Gan, Israel) [15], which utilizes artificial intelligence algorithms to provide nociception scores ranging from 0 to 100. Using a non-invasive finger probe connected to the PMD-200 monitor, it evaluates photoplethysmography, galvanic skin response, accelerometry, and skin temperature to generate its output. While the NOL index has been validated for use in anesthetized patients undergoing surgery [16], its application in awake surgical populations remains largely unexplored. Investigating its use in this setting is relevant for several reasons. Firstly, awake patients under regional anesthesia with sedation may still experience nociception or discomfort, even if they do not fully verbalize it. Secondly, correlation between NOL trends and patient distress or sedation self-administration could suggest a role for NOL as an early indicator for sedation adjustments. Finally, studying the NOL index in awake patients offers a unique opportunity to compare objective nociception data with real-time subjective patient feedback.

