#### 2.1.4. Outcomes.

The primary outcome is the time-adjusted and weight-adjusted average or median self-administered dose of propofol in mcg/kg/min.

Secondary outcomes include

Initial enthusiasm at the idea of using a VR headset during surgery assessed by research staff on a 10-point Likert scale for all participants, prior to intervention allocation as part of a questionnaire;Level of anxiety and information requirement measured preoperatively by research staff using the Amsterdam Preoperative Anxiety and Information Scale (APAIS) [18];Incidence of intraoperative and postoperative adverse events such as bradycardia (heart rate < 50 bpm), desaturation (SpO_2_ < 92%) and hypotension (MAP < 60) as well as subjective adverse events, such as cybersickness or nausea documented intraoperatively by the anesthesiologist and research staff based on real-time clinical observation or patient self-reporting;Average or median total time, in minutes, during which the VR headset was worn, as well as the percentage of that time relative to the overall duration of the surgery, recorded by dedicated research staff in the operating room using a time log;Average or median total duration in minutes spent by the patient on the VR scenario chosen, and the order in which VR scenarios were presented, recorded by dedicated research staff in the operating room using a time log and a case report form (CRF);Percentage of patients that switched scenarios;Percentage of patients that removed the headset before the end of the surgery;Percentage of patients requiring additional local anesthesia;Weight-adjusted average or median administration of intraoperative IV fentanyl in mcg/kg;Weight-adjusted average or median administration of intraoperative IV ketamine in mg/kg;PACU length of stay (LOS) measured from PACU admission to PACU discharge, based on the PACU nursing records;Ease of use of the technology and enjoyment of the first scenario chosen assessed post-operatively on a 10-point Likert scale in the intervention group only as part of a postoperative questionnaire administered by dedicated research staff;Overall satisfaction with the experience assessed post-operatively on a 10-point Likert scale in both groups as part of a postoperative questionnaire administered by dedicated research staff.Exploratory outcomesNOL index readings over time per patient, recorded continuously intraoperatively via a finger probe, automatically stored and extractable by dedicated research staff from the PMD-200 monitor with precise timepoints. NOL index spikes will be defined;PCS bolus administration timepoints, automatically recorded by the pump device and extracted by dedicated research staff.

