
Exploratory analysis will focus on evaluating NOL trends over time and assessing whether NOL peaks are associated with PCS administration timepoints.

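### The exploratory NOL bolus-prediction analysis uses a single absolute cut at 50 as its only predictor, and the protocol gives no basis for that cut in awake patients

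*Protocol article*

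**What the plan says.** Section 1.1 (Background and rationale) of the protocol article describes an index that "utilizes artificial intelligence algorithms to provide nociception scores ranging from 0 to 100". On its evidence base the same section says: "While the NOL index has been validated for use in anesthetized patients undergoing surgery [16], its application in awake surgical populations remains largely unexplored". Section 1.2 makes the study of NOL in awake patients, including its ability to anticipate self-administered sedation, an exploratory objective.

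Section 2.1.4 (Outcomes) lists two exploratory data streams: NOL readings stored continuously with exact times, and the times of the patient-controlled sedation (PCS) boluses as logged by the pump. It leaves the event itself open ("NOL index spikes will be defined") and adds: "Exploratory analysis will focus on evaluating NOL trends over time and assessing whether NOL peaks are associated with PCS administration timepoints".

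Section 2.3.3 (Statistical methods) then supplies the definition: "we will define a spike as any NOL score exceeding a threshold of 50 for a pre-specified duration of at least 10 seconds". Logistic regression and/or time-to-event analysis is to be used to "determine whether NOL spikes significantly predict the likelihood of a propofol bolus within a predefined timeframe of up to 60 seconds". That prediction analysis has no alternative threshold, no change relative to the patient and no continuous NOL term. No reason for 50 is stated.

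**The concern.** The cut is absolute and the same for every patient, in a setting where the protocol itself says little is known about the index. Nothing in the document shows where awake readings usually lie, so nothing shows that 50 separates quiet periods from nociceptive ones.

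Two consequences follow. First, if most readings fall on one side of 50, the spike hardly varies and cannot predict much, whatever the index itself contains. Second, a yes/no spike at a common level does not distinguish a patient whose NOL is generally high from one whose NOL has just risen. Anticipating a bolus depends on the second.

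What is at stake is how the exploratory result can be read. A null finding would be ambiguous between an uninformative index and a misplaced cut, although the continuous trace that could help to tell them apart is already being stored.

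**Working it through.** **1. Is there a figure to reproduce?** No. The protocol gives no expected spike rate, no awake NOL mean or SD, and no power statement for this aim. Everything numerical below rests on assumed awake distributions and shows a range, not an estimate.

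**2. How often would a spike occur?** Inputs from section 2.3.3: cut 50, run of at least 10 s, 60-s window. Assumed: normal readings with mean 20 to 70 and SD 10 or 15, one reading per second, a 90-minute operation, first-order autocorrelation with a correlation time of 20 or 60 s, and 200 simulated traces that all share the same mean and SD.

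Share of readings above 50 = 1 − Φ((50 − mean)/SD). For example, with mean 30 and SD 15, (50 − 30)/15 = 1.33, which gives 9.1%. The last column is the simulated share of 60-s windows in which a run above 50 reaches 10 s. Its range covers the two correlation times.

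| Assumed mean / SD | Readings above 50 | 60-s windows with a spike |
|---|---|---|
| 20 / 10 | 0.13% | 0.1–0.2% |
| 20 / 15 | 2.3% | 3.2–4.2% |
| 30 / 15 | 9.1% | 15.6–15.7% |
| 40 / 15 | 25.3% | 39.8–43.4% |
| 50 / 15 | 50% | 69.4–76.6% |
| 60 / 10 | 84.1% | 95.2–98.3% |
| 70 / 10 | 97.7% | 99.8–100% |

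With mean 20 and SD 10, 85% to 94% of simulated patients never had a spike. With a mean of 60 or 70 and SD 10, nearly every window had one. With means of 30 to 50 and SD 15, neither extreme occurs. The protocol does not say which row applies.

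**3. What does a cut cost?** For one normally distributed reading with a linear effect, the efficiency of the dichotomised predictor relative to the continuous one is φ(z)² / (p(1 − p)), where p is the share of readings above the cut and z is the (1 − p) normal quantile.

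- p = 50%: 0.3989² / 0.25 = 0.64
- p = 10%: 0.1755² / 0.09 = 0.34
- p = 5%: 0.22
- p = 2%: 0.12
- p = 1%: 0.07

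The values are the same for shares of 1 − p. The best case, a cut at the median, keeps about 64%.

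**4. Does the plan elsewhere link continuous NOL to boluses?** Section 2.1.4 plans two things: NOL trends over time, and an association between peaks and PCS times. The trends are not tied to boluses. The link to boluses runs through peaks in 2.1.4 and through spikes in 2.3.3, and 2.3.3 defines the spike by the single cut.

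**The case against.** The strongest defence is that the aim is exploratory, that an event definition suits a question about early warning, and that fixing one threshold and duration in advance prevents a later search for the cut that works. All of this stands, and it is why the spike analysis should be kept. It is also fair that sensitivity analyses are often left to an analysis plan, which is not shown. But the article does not leave the predictor open: it fixes one.

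Several stronger readings are tempting, and the documents do not support them.

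- *That the spike will be almost never or almost always present.* This needs an awake NOL distribution that the protocol does not give. Mid-range assumptions in the table avoid both extremes.
- *That the whole NOL analysis is reduced to a cut.* Section 2.1.4 also plans trends over time. Only the bolus prediction is affected, and no data are lost, because the traces are stored.
- *That the index is validated in anesthetized patients alone.* Section 1.1 reports validation in those patients and calls awake use largely unexplored. It does not say more than that.
- *That a stated share of the information will be lost.* The efficiency formula describes a single normal reading. The planned predictor is a run of at least 10 s in serially correlated data, with a binary or time-to-event outcome. The figures are arithmetically right but do not measure the loss in this analysis. If boluses follow abrupt events rather than a gradient, the formula's premise of a linear effect fails.

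One obvious remedy also has faults. Change from a pre-incision value, averaged over 60 s, would dilute a short rise: 40 points for 10 s moves a 60-s mean by 40 × 10/60 = 6.7 points. Under section 2.1.3 (Interventions), sedation and analgesia precede the block, and VR starts when the surgeon is ready for disinfection. A pre-incision value may therefore follow sedation and, in one arm, the start of the randomized intervention.

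**Conclusion.** The point holds for the bolus-prediction analysis in section 2.3.3 and is minor. The only predictor there is one absolute cut, with no stated basis in a population for which the protocol calls the index largely unexplored. As planned, a null result could not separate a failure of the index from a failure of the cut.

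Its size is unknown. Across the assumed distributions, the share of windows with a spike runs from about 0.1% to 100%. The ceiling of about 64% on retained information applies only to a single normal reading with a linear effect, and is illustrative. The primary outcome, the sample size and the conclusions about VR do not depend on this analysis.

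**What to change.** In section 2.3.3, keep the pre-specified spike analysis unchanged and add three items.

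1. In the same logistic or time-to-event model, enter NOL as a continuous, time-varying predictor, for example its maximum or mean over a short preceding window. State the window in advance.
2. Split that predictor into the patient's own average level and the deviation from it, so that within-patient change is estimated separately from differences between patients. This avoids relying on a pre-incision baseline.
3. Report the share of time each patient spends above 50, so that readers can see whether the cut was informative in awake patients.

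The NOL readings and bolus times are already to be recorded, so no new data are needed. The cost is a few sentences, a little programming and one more exploratory result to report. The change should be made before the NOL data are analysed, so that the added predictor is as clearly pre-specified as the spike.

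### The exploratory NOL question is whether the index can anticipate a self-administered bolus, but the only stated criterion is a significance test, which does not measure anticipation

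*Protocol article*

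**What the plan says.** Section 1.2 gives the exploratory objective as the use of NOL in awake surgical patients and "the ability to anticipate sedation self-administration via the NOL index". The rationale in section 1.1 says that a correlation between NOL trends and distress or self-administration "could suggest a role for NOL as an early indicator for sedation adjustments". Section 2.1.4 words the analysis more modestly, as "assessing whether NOL peaks are associated with PCS administration timepoints".

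Section 2.3.3 returns to prediction. The aim there is to "determine whether NOL spikes serve as a predictor of subsequent propofol boluses". The team will "define a spike as any NOL score exceeding a threshold of 50 for a pre-specified duration of at least 10 seconds" and examine the temporal relationship by time-series methods. The step after that is to "apply logistic regression and/or time-to-event analysis". The criterion given for this regression step reads as follows: "determine whether NOL spikes significantly predict the likelihood of a propofol bolus within a predefined timeframe of up to 60 seconds". Earlier in the same section, "statistical significance will be determined using an alpha level of 0.05". The one check named specifically for logistic models is the Hosmer-Lemeshow test.

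**The concern.** Anticipation has two parts: how many boluses are preceded by a spike, and how many spikes are followed by a bolus. A significant regression coefficient answers neither. It says that bolus risk differs after a spike, and its p-value depends on the number of windows, the event rates and the within-patient correlation as well as on the strength of the marker.

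This goes beyond detail left to an analysis plan. Section 2.3.3 already fixes the spike threshold, its minimum duration, the prediction horizon, the model family and the word that defines success. The criterion so fixed does not match the objective in section 1.2.

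At stake is the reading of one exploratory result. The protocol describes NOL use in awake surgical patients as largely unexplored, so readers could take a significant coefficient as early support for a warning role when the same data show poor discrimination. They could equally take a non-significant one as evidence against that role.

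**Working it through.** The document gives no figure for the NOL analysis, so there is none to reproduce. The check is whether significance and discrimination can separate under plausible inputs.

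**From the protocol:** 100 patients; 60-second horizon; alpha 0.05; 0.15 mg/kg boluses with a 2-minute lockout (section 2.1.3); historical median propofol dose of 525 mg per patient (section 2.1.6).

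**Assumed:** 90 minutes of surgery, so 100 × 90 = 9,000 one-minute windows; 500 with a spike and 8,500 without; the bolus rates below; a design effect of 3 for clustering within patients.

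**Formulas:** z = (p1 − p0) / √[p(1 − p)(1/500 + 1/8,500)], with p the pooled bolus rate, divided by √3 for clustering. Sensitivity = bolus windows with a spike / all bolus windows. Specificity = bolus-free windows without a spike / all bolus-free windows. AUC of a binary marker = (sensitivity + specificity) / 2.

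**Scenario A, 10% against 5%**
- Boluses: 500 × 0.10 = 50 and 8,500 × 0.05 = 425. Pooled rate 475/9,000 = 0.0528.
- OR = (50/450)/(425/8,075) = 2.1. z = 0.05/0.01029 = 4.86; with clustering 2.81, P = 0.005.
- Sensitivity 50/475 = 10.5%; specificity 8,075/8,525 = 94.7%; PPV 10%; AUC 0.526.

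**Scenario B, 20% against 5%**
- OR 4.75; z = 0.15/0.01079 = 13.9; with clustering 8.0.
- Sensitivity 100/525 = 19%; specificity 8,075/8,475 = 95.3%; PPV 20%; AUC 0.572.

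**Scenario C, frequent boluses**
- The historical 525 mg equals 525/(0.15 × 90) = 39 to 525/(0.15 × 60) = 58 bolus-equivalents at assumed weights of 90 and 60 kg. The lockout allows about 90/2 = 45 in 90 minutes. Scenario A implies only 475/100 = 4.75 per patient, so a much higher rate must be tried.
- Take 40% in non-spike windows and OR 2. Spike-window odds are 2 × 0.40/0.60 = 1.333, so PPV = 1.333/2.333 = 57%.
- Boluses: 500 × 0.571 = 286 and 8,500 × 0.40 = 3,400, or 3,686/100 = 36.9 per patient. Base rate 3,686/9,000 = 41%.
- z = 0.171/0.0226 = 7.6; with clustering 4.4.
- Sensitivity 286/3,686 = 7.8%; specificity 5,100/5,314 = 96.0%; AUC 0.519.

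PPV runs from 10% to 57% across the scenarios, while AUC stays between 0.52 and 0.57.

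**The reverse direction.** Keep 9,000 windows, with spikes in 5%, boluses in 5% and OR 1.5. A Wald test of the log odds ratio gives z = 2.14, P = 0.033 with independent windows, and z = 1.07, P = 0.29 with a design effect of 4. Sensitivity (7.2%) and AUC (0.511) are identical in both. The p-value crosses 0.05 while discrimination does not move.

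**Wider range.** For bolus rates of 5–20%, spikes in 5–10% of windows, OR 1.5–2.0 and design effects of 1–4, P runs from 3 × 10⁻¹⁹ to 0.29, sensitivity from 7 to 18%, PPV from 7 to 32% and AUC from 0.51 to 0.54.

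**Fit check.** Hosmer-Lemeshow tests calibration, not discrimination. With a single binary predictor the model reproduces its two observed proportions exactly, so the test has nothing to detect.

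**Lockout.** At 2 minutes it is longer than the 60-second horizon. A spike in the first minute after a bolus cannot be followed by a delivered self-administered bolus within its window. In scenario A about 4.75 × 2 = 9.5 of 90 minutes are locked out; in scenario C about 36.9 × 2 = 74 of 90. The scenarios above ignore this, but the real analysis cannot.

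**The case against.** The strongest reply is that this is an exploratory analysis described in a journal article, with the analysis plan not shown. Performance measures are often left to that plan, and the protocol excludes none. Section 2.3.3 also speaks of investigating a relationship and plans a time-series step first. Section 2.1.4 asks only about association, and the rationale in section 1.1 is hedged. The wording about significant prediction is ordinary regression language, and the model will yield an odds or hazard ratio as well as a p-value.

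Much of this stands. A reader might infer that no measure of prediction will be calculated, or that a useless alarm would be reported as predictive. The document supports neither: it has no rule that P < 0.05 alone decides the conclusion, and it cannot show what an unseen plan contains. A reader might also infer that most alarms would be false. That follows only from a low assumed bolus rate, and scenario C removes it. The historical 525 mg need not have been self-administered, so it is a rough anchor only, but it prevents treating the low rate as the expected one.

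What does not fall is the mismatch in the text. Sections 1.2 and 2.3.3 ask about anticipating and predicting, and the one criterion stated is significance. An odds ratio does not close the gap: in scenario B an OR of 4.75 goes with 81% of boluses missed. If association is all that is meant, the prediction wording overstates the analysis.

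**Conclusion.** The concern holds as a mismatch between an exploratory objective and its stated criterion. A significant coefficient could coexist with near-chance discrimination (AUC 0.52 to 0.57 in the three scenarios, with z at least 2.8 after a design effect of 3), and a non-significant one would not answer the question either. That the two questions separate is a matter of logic. The sizes are illustrative and rest on assumed surgery length, spike frequency, bolus rates and clustering. The low AUC is the steadier feature of the illustration; PPV is not stable.

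A highly significant result is possible, not expected. The point touches no primary or secondary conclusion, and nothing in the trial's conduct acts on NOL. It is worth correcting before analysis because the remedy is cheap and avoids choosing performance measures after seeing the data.

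**What to change.** In section 2.3.3, replace significance as the basis for any statement about anticipation with:

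- sensitivity, PPV set against the base rate, false alarms per hour, and AUC (or time-dependent AUC), each with a 95% confidence interval from a bootstrap that resamples patients;
- the odds or hazard ratio as supporting evidence, with standard errors that allow for repeated windows within patients;
- a 60-second window that starts when the 10-second spike criterion is met, so that only information available beforehand is used;
- an explicit lockout rule for the analysis: limit it to time when a bolus is available by excluding time inside the 2-minute lockout, or use recorded button presses as the event if the pump logs them. Without such a rule, spikes during lockout would count as false alarms whatever the merit of the index.

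The cost is a few lines of text and a little more analysis work on an exploratory objective. The continuous NOL readings and pump-recorded bolus times are already planned in section 2.1.4. The primary outcome is unaffected.
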